**Study schedule**

| Phase                           | Study visit | Treatment period |         |         | Follow-up period |         |         |
|---------------------------------|-------------|------------------|---------|---------|------------------|---------|---------|
| Visit                           | Enrollment  | Visit 1          | Visit 2 | Visit 3 | Visit 4          | Visit 5 | Visit 6 |
| Timing                          | Day 0       | Day 3            | Week 1  | Week 2  | Week 6           | Week 14 | Week 26 |
| Baseline data            |             |                  |         |         |                  |         |         |
| Inclusion criteria confirmation | √           |                  |         |         |                  |         |         |
| Exclusion criteria confirmation | √           |                  |         |         |                  |         |         |
| Informed consent obtained       | √           |                  |         |         |                  |         |         |
| Demographic data collected      | √           |                  |         |         |                  |         |         |
| Efficacy assessments     |             |                  |         |         |                  |         |         |
| ODI                             | √           | √                | √       | √       | √                | √       | √       |
| Leg pain VAS                    | √           | √                | √       | √       | √                | √       | √       |
| Low back pain VAS               | √           | √                | √       | √       | √                | √       | √       |
| SF-12                           | √           | √                | √       | √       | √                | √       | √       |
| Safety monitoring        |             |                  |         |         |                  |         |         |
| Complete blood count            | √           |                  |         | √       |                  |         |         |
| Liver function tests            | √           |                  |         | √       |                  |         |         |
| Renal function tests            | √           |                  |         | √       |                  |         |         |

|                          |   |   |   |   |  |  |   |
|--------------------------|---|---|---|---|--|--|---|
| Adverse events recording |   | √ | √ | √ |  |  |   |
| Imaging           |   |   |   |   |  |  |   |
| X-ray                    | √ |   |   |   |  |  |   |
| CT                       | √ |   |   |   |  |  |   |
| MRI                      | √ |   |   |   |  |  | √ |

## **7. AEs observation and analysis**

An AE will refer to any untoward medical occurrence in a patient administered a pharmaceutical product or medical intervention, which does not necessarily have a causal relationship with the treatment. AEs will encompass abnormal laboratory findings, ADRs, anticipated adverse effects of the investigational therapy, and events where causality assessment will be required. All AEs will be managed and reported in accordance with established regulatory and ethical guidelines.

### **7.1. Criteria for AE assessment**

Common AEs will include:

(1) LOPM-related: Worsening low back pain, restricted lumbar mobility, aggravated lower limb numbness or pain.

(2) Drug-related: Gastrointestinal reactions (e.g., constipation, epigastric pain, nausea, vomiting), allergic reactions (e.g., skin rash, urticaria), and other side effects such as physical dependence or drug tolerance.

SAEs will be defined as progressively worsening symptoms, including:

- (1) Muscle weakness.
- (2) Cauda equina syndrome.
- (3) Severe intractable pain.

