## **5. Treatment**

### **5.1. Treatment protocol**

Participants will be randomly assigned in a 1:1:1 ratio to one of three treatment groups: (1) The YBT group: YBT capsules will be administered orally. (2) The LOPM group: LOPM will be performed. (3) The YBT + LOPM group: Participants will receive both YBT capsules and LOPM. In addition to their assigned treatments, all participants will perform standardized lumbar functional exercises throughout the treatment period.

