## 6.2. Safety assessment

Blood routine tests and liver and kidney function tests were conducted before randomization and at 2 weeks after randomization. In addition, detailed records of each patient's gastrointestinal discomfort, skin allergies, and other AEs were collected at 2 weeks after randomization to assess safety.

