### **7.3. Documentation of Common AEs**

All AEs will be recorded following each treatment session. Particular attention will be given to:

- (1) LOPM-related AEs (e.g., symptom exacerbation).
- (2) Drug-related AEs (e.g., gastrointestinal disturbances, cutaneous allergic reactions).
- (3) Other potential treatment-emergent AEs, which will be actively solicited and documented.

For each AE, the following details will be collected:

- (1) Clinical manifestations.
- (2) Severity (mild/moderate/severe).
- (3) Onset date.
- (4) Duration.
- (5) Resolution date.
- (6) Interventions applied.
- (7) Assessed causality to treatment (definite/probable/possible/unlikely/unrelated);
- (8) Outcome.

A comprehensive analysis will be performed, accounting for comorbidities and concomitant therapies, to evaluate their association with the study treatment. These data will be used to systematically characterize:

- (1) Complications.
- (2) Contraindications.
- (3) Indications.

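### Symptom worsening is pre-labelled as LOPM-related, is not named in the week-2 safety record, and can be recorded on more occasions in the LOPM arms, so the between-arm adverse event comparison is open to differential ascertainment and attribution

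*Protocol*

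**What the plan says.** Section 7 of the protocol defines an adverse event without regard to cause: "An AE will refer to any untoward medical occurrence in a patient administered a pharmaceutical product or medical intervention". It adds that no causal link is needed. Section 7.2 then has the causality of each event graded on five levels.

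Section 7.1 groups the common events by treatment. One group is "LOPM-related: Worsening low back pain, restricted lumbar mobility, aggravated lower limb numbness or pain". The other is "Drug-related: Gastrointestinal reactions (e.g., constipation, epigastric pain, nausea, vomiting), allergic reactions (e.g., skin rash, urticaria), and other side effects such as physical dependence", and tolerance is listed there as well. Section 7.3 asks for particular attention to the same two groups, with symptom exacerbation as the example for LOPM, and adds a third, residual item for other treatment-emergent events, which are to be actively solicited. Section 7.3 also has events recorded after every treatment session.

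The safety record for all arms is described in section 6.2: "detailed records of each patient's gastrointestinal discomfort, skin allergies, and other AEs were collected at 2 weeks after randomization to assess safety". The Endpoints and Safety indicators rows of the Summary and section 6.1 say the same. The Study schedule table has adverse event recording at Day 3, Week 1 and Week 2 for everyone.

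Section 5.1 states that "all participants will perform standardized lumbar functional exercises throughout the treatment period". Section 6.1 makes adverse events a secondary outcome, and section 10.6 compares categorical outcomes between groups by chi-square or Fisher's exact test with Bonferroni correction.

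**The concern.** Worsening back or leg symptoms are not specific to manipulation. They can come from the natural course of the disease, from lack of effect, or from the exercises that every arm performs. Yet the protocol names this worsening as a harm only under an LOPM heading. In a patient on YBT alone, staff have no named line for it. Section 11.3.2 also lists failure to obtain symptom relief as a disease-progression risk, which makes it easy to read worsening under YBT as lack of efficacy and not to record it as an adverse event.

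Two further features can make capture unequal. Recording after each session gives the two LOPM arms extra occasions. The week-2 record, in contrast, names the main drug-type harms and none of the LOPM-type harms, so prompting there favours detection of drug-type events.

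At stake is the validity of the adverse event comparison. Fuller counting of worsening in the LOPM arms would make the combination look more harmful than YBT alone. Weak prompting for worsening at week 2 would understate a true manipulation harm. These act in opposite directions, so the net error could not be predicted or removed afterwards.

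**Working it through.** **1. Where symptom worsening stands in each arm**

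| Place in protocol | LOPM and YBT + LOPM arms | YBT arm |
|---|---|---|
| Section 7 definition | adverse event | adverse event |
| Section 7.1 common events | named | no named heading |
| Section 7.3 attention list | named (symptom exacerbation) | residual item, actively solicited |
| Section 6.2 week-2 record | residual item | residual item |
| Section 7.1 serious events, if progressive | covered | covered |

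The event is recordable in every arm. What differs is whether it is named and to what it is attributed.

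**2. Recording occasions in the 2-week treatment period**

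- Scheduled visits, all arms (Study schedule): Day 3, Week 1, Week 2 = 3.
- LOPM sessions (section 5.1, LOPM technique; Summary, Study duration): 3 per week x 2 weeks = 6.
- LOPM arms: 6 occasions if every visit falls on a session day, and 6 + 3 = 9 if none does.
- YBT arm: 3, since no sessions are described for oral treatment.

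**3. Illustration of the consequence**

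The protocol states no figure to reproduce here: it gives no adverse event rate and no capture rate. The only documented input is 146 participants per group (section 3.2). The following are assumptions:

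- the true worsening rate r is equal in the two arms compared;
- all events are captured in an LOPM arm and a fraction k in the YBT arm;
- alpha is 0.05/3 = 0.0167, for three pairwise comparisons. Section 10.6 names Bonferroni but not the divisor.

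The apparent risk ratio is r/(k x r) = 1/k, and the expected number of missed YBT-arm events is 146 x r x (1 - k). The chance of a significant Pearson chi-square result was found by summing the two binomial distributions, Bin(146, r) and Bin(146, k x r), over all tables that reject.

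| k | Apparent risk ratio, 1/k | Missed events at r = 10% | P(significant), r = 5% | r = 10% | r = 15% |
|---|---|---|---|---|---|
| 1 (equal) | 1.00 | 0 | 1.3% | 1.6% | 1.6% |
| 0.90 | 1.11 | 146 x 0.10 x 0.10 = 1.5 | 1.4% | 2.0% | 2.3% |
| 0.75 | 1.33 | 146 x 0.10 x 0.25 = 3.7 | 2.4% | 4.7% | 7.2% |
| 0.50 | 2.00 | 146 x 0.10 x 0.50 = 7.3 | 7.7% | 20.6% | 35.6% |

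Small differences in capture do almost no harm. Large ones produce a spurious difference often. The protocol does not say which applies.

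**The case against.** A reader might infer that worsening in the YBT arm has no category at all and that the harm comparison is therefore biased. The documents do not support that. Worsening under YBT is an adverse event by the section 7 definition, it comes under the actively solicited residual item in section 7.3, and it is a serious event in any arm if progressive (section 7.1). The week-2 record is not confined to drug-type harms, because each version ends with other events. It also leaves out one drug item, dependence or tolerance.

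The case against goes further. The section 7.1 list can be read as anticipated events, with causality still graded per event in section 7.2. The attention list in section 7.3 is not split by arm, and the three scheduled visits are common to all. ODI and both pain scales are collected at every time point in all arms, and section 8.1 has evaluators masked.

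Much of this stands, and it limits the point to a risk. It does not remove it. A residual line is a weaker prompt than a named one, and an event never recorded as adverse is never graded for causality. Masking in section 8.1 concerns outcome assessment; the protocol does not say that masked evaluators collect adverse events, and recording after a manipulation session implies knowledge of treatment. ODI and pain scores would show average worsening but do not supply adverse event counts.

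**Conclusion.** The point holds as a risk of differential ascertainment and attribution in one secondary outcome. It rests on three features of the text: worsening is named by symptom type under LOPM only, the week-2 record does not name it, and session-based recording gives the LOPM arms 6 to 9 occasions against 3. The labelling also sits badly with the protocol's own cause-neutral definition and per-event causality grading.

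Neither the direction nor the size of any bias can be stated. The table above is conditional on assumed rates and on an assumed divisor of 3. If capture is equal there is no bias, and at 90% capture the false-positive rate is barely raised. The figure of about 21% at 50% capture is an adverse case, not an estimate. The primary ODI analysis and the sample size are not affected.

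**What to change.** - **Sections 7.1 and 7.3:** replace the two treatment-based headings with cause-neutral groups: musculoskeletal or neurological worsening; gastrointestinal, allergic and other.
- **Elicitation:** use one identical named event list in all three arms at Day 3, Week 1 and Week 2. Name symptom worsening in the Summary (Endpoints and Safety indicators rows), section 6.1 and section 6.2.
- **Comparison:** base the between-arm analysis on all-cause events by arm in the safety analysis set, taken from those common visits. Keep recording events after LOPM sessions, but report the additional events found there descriptively.
- **Causality:** keep the per-event grading of section 7.2 as a separate, descriptive step.

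The cost is wording in the listed places and a revised adverse event page of the CRF; no new visits are needed. The downside is that more symptom-worsening events will be reported, mainly in the YBT arm.

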### **7.2. Analysis of causality and severity**

All AEs will be systematically documented, and their association with the treatment will be assessed. Causality will be classified according to the Guidelines for Clinical Research of New Traditional Chinese Medicine Drugs (Trial) into five categories:

- (1) Definite.
- (2) Probable.
- (3) Possible.
- (4) Unlikely.
- (5) Unrelated.

Severity will be graded as follows:

- (1) Mild: No significant impact on daily activities (work or study).
- (2) Moderate: Interference with daily activities.
- (3) Severe: Marked limitation of daily activities.

All AEs will be recorded along with the corresponding management measures and treatment outcomes.

### **7.3. Documentation of Common AEs**

All AEs will be recorded following each treatment session. Particular attention will be given to:

- (1) LOPM-related AEs (e.g., symptom exacerbation).
- (2) Drug-related AEs (e.g., gastrointestinal disturbances, cutaneous allergic reactions).
- (3) Other potential treatment-emergent AEs, which will be actively solicited and documented.

For each AE, the following details will be collected:

- (1) Clinical manifestations.
- (2) Severity (mild/moderate/severe).
- (3) Onset date.
- (4) Duration.
- (5) Resolution date.
- (6) Interventions applied.
- (7) Assessed causality to treatment (definite/probable/possible/unlikely/unrelated);
- (8) Outcome.

A comprehensive analysis will be performed, accounting for comorbidities and concomitant therapies, to evaluate their association with the study treatment. These data will be used to systematically characterize:

- (1) Complications.
- (2) Contraindications.
- (3) Indications.

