## (2) LOPM technique

The LOPM will be performed 3 times per week. The general procedure will be as follows: First, assess the tension of the soft tissues to identify the location of the lesion. Then, apply lumbar tendon-regulation techniques, which include four methods: palm-pressing, finger-kneading, shoulder-pulling and lumbar-pushing, and leg-pulling and lumbar-pushing. Use palm-pressing and finger-kneading to relax spasming lumbar muscles, focusing on loosening local tender points. Follow this with tendon-regulation techniques such as shoulder-pulling and lumbar-pushing or leg-pulling and lumbar-pushing to fully stretch the spine and further relax the surrounding soft tissues. Next, perform the step-by-step oblique pull manipulation. Finally, conduct a quality check of the manipulation.

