### (3) Lumbar functional exercise routine

The lumbar functional exercise routine will be performed twice daily (once in the morning and once in the afternoon), consisting of five movements: rotational stretch, swallow dive, supine bridge, knee-to-chest curl, and air cycling. Each session will last 10 minutes.

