## **6. Observation endpoints and clinical outcomes**

### **6.1. Clinical observation endpoints**

Efficacy measures will be recorded at baseline and 3 days, 1 week, 2 weeks, 6 weeks, 14 weeks, and 26 weeks after randomization. The measurement instruments will be ODI for the functional disability, VAS for the leg and low back pain, and 12-Item Short Form Health Survey (SF-12) for the quality of life. Blood routine tests and liver and kidney function tests will be conducted before randomization and at 2 weeks after randomization. In addition, detailed records of each patient's gastrointestinal discomfort, skin

allergies, and other adverse events will be collected at 2 weeks after randomization to assess safety. At the 26-week post-randomization follow-up, a repeat MRI will be performed. The change in the sagittal area of the disc herniation from baseline to 26 weeks will be measured, with a reduction of  $\geq 40\%$  defined as the occurrence of disc resorption. The disc resorption rates will be calculated. The primary outcome will be change in ODI from baseline to week 2. The minimal clinically important difference (MCID) for ODI will be set at  $\geq 7$  points, consistent with prior studies. Secondary outcomes will include leg and low back pain VAS, SF-12, adverse events, and disc resorption rates.

(1) ODI

ODI assesses the effect of pain on normal daily activity including the ability to and intensity of lifting, care for oneself, walk, sit, sexual function, stand, social life, sleep and travel, ranging from 0 (no disability) to 100 (maximum disability possible).

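### The protocol gives three conflicting rules for when adverse events are recorded; one of them gives the two LOPM arms more recording occasions than YBT alone, and no routine recording is scheduled after Week 2

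*Protocol*

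**What the plan says.** The protocol sets the timing of adverse-event (AE) recording in several places, and they differ.

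- **Summary (Endpoints and Safety indicators rows), Sections 6.1 and 6.2:** a single collection point. Section 6.1 has "allergies, and other adverse events will be collected at 2 weeks after randomization to assess safety"; Section 6.2 has "skin allergies, and other AEs were collected at 2 weeks after randomization to assess safety".
- **Study schedule (end of Section 6.3):** the row "Adverse events recording" is ticked at Day 3, Week 1 and Week 2 for all participants. It is blank at Weeks 6, 14 and 26.
- **Section 7.3:** "All AEs will be recorded following each treatment session". It adds that other treatment-emergent events will be actively asked for.

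Treatment contact differs by arm. For manipulation, "The LOPM will be performed 3 times per week", and the Summary gives a 2-week treatment period. For YBT alone, Section 5.1 says "1) The YBT group: YBT capsules will be administered orally", and no practitioner session is described. All arms also do the lumbar exercises twice daily, of which the protocol says "Each session will last 10 minutes".

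AEs are a named secondary outcome (Section 6.1), and the safety of the combination is a stated aim (Section 1). Categorical outcomes are compared between groups by chi-square or Fisher's exact test with a Bonferroni correction (Section 10.6).

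Some reporting duties carry no end date: serious events within 24 hours and as-needed health assessments (Section 5.6), and notification of all AEs within 24 hours (Section 7.4). Section 4.5 continues safety monitoring of discontinued participants until open events settle.

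**The concern.** Two things are at stake.

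The first is comparability. If recording is tied to treatment sessions, and only two arms have sessions with a practitioner, those arms are observed more often. The same true event rate can then give more recorded events there. Short-lived events are the most exposed: Section 7.4 says that reactions to LOPM typically settle in 24 to 48 hours, so an event may be seen at a session yet be over, and perhaps not reported, by the next visit. The events that Section 7.1 lists as LOPM-related (worse back pain, restricted mobility, more limb numbness or pain) are also symptoms of the disease and can occur under YBT alone. Gastrointestinal events from the same capsules would be recorded at more occasions in the combination arm than in the YBT arm. Combination versus YBT is one of the two primary comparisons in Section 3.2, so readers will look to its safety side.

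The second is coverage. Participants attend at Weeks 6, 14 and 26 for efficacy measures, but nothing at those visits prompts the AE question.

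With 13 hospitals and no statement of precedence, sites could reasonably follow different rules. Randomization is stratified by centre, so differences between sites are spread across the arms. The session rule, however, separates the arms within every site that follows it.

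**Working it through.** The protocol states no figure for the AE comparison, so there is none to reproduce. The check is a count of recording occasions, followed by an illustration of what unequal counts could do.

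**Inputs from the protocol**
- LOPM: 3 sessions per week (Section 5.1.1, LOPM technique); treatment period 2 weeks (Summary)
- Scheduled AE recording: Day 3, Week 1, Week 2 (study schedule)
- Follow-up: 2 + 24 = 26 weeks (Summary)
- 146 participants per group (Section 3.2)

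**Step 1: occasions to Week 2.** LOPM sessions = 3 × 2 = 6 in each LOPM arm. Reading a treatment session as a practitioner-delivered one, YBT alone has 0.

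| Rule followed | YBT | LOPM | YBT + LOPM |
|---|---|---|---|
| Week 2 only (Summary, 6.1, 6.2) | 1 | 1 | 1 |
| Schedule | 3 | 3 | 3 |
| Schedule plus 7.3, no session on a visit day | 3 | 3 + 6 = 9 | 9 |
| Schedule plus 7.3, three sessions on visit days | 3 | 3 + 6 − 3 = 6 | 6 |

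Under the schedule plus Section 7.3, the contrast is 3 against 6 to 9. LOPM and YBT + LOPM are equal under every rule.

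**Step 2: routine coverage.** (26 − 2)/26 = 24/26 = 92% of follow-up has no scheduled AE recording, and 3 of the 6 post-baseline visits carry no tick.

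**Step 3: illustration.** Assumptions, none from the protocol: the same true AE risk *r* in every arm; each contact independently picks up an event with probability *p*; every event has all *k* contacts available to it. Then

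recorded rate = *r* × [1 − (1 − *p*)^*k*]

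The ratio of recorded rates, LOPM arms to YBT, does not depend on *r*:

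| *p* | 6 v 3 contacts | 9 v 3 contacts |
|---|---|---|
| 0.2 | 1.51 | 1.77 |
| 0.3 | 1.34 | 1.46 |
| 0.5 | 1.12 | 1.14 |
| 0.8 | 1.01 | 1.01 |

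Take *r* = 10% and *p* = 0.3:
- *k* = 3: 10% × (1 − 0.7³) = 10% × 0.657 = 6.6%
- *k* = 6: 10% × (1 − 0.7⁶) = 10% × 0.882 = 8.8%
- *k* = 9: 10% × (1 − 0.7⁹) = 10% × 0.960 = 9.6%

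For 9 v 3 with 146 per arm, the difference is 0.030 and its standard error is √[(0.066 × 0.934 + 0.096 × 0.904)/146] = 0.032. The chance of a significant excess in a LOPM arm, when true risks are equal, is Φ(0.95 − 1.96) = Φ(−1.01), about 16%, against a nominal upper-tail 2.5%. At a level of 0.05/3 (assuming that the Bonferroni correction covers three pairwise comparisons) it is about 7% against 0.8%. For 6 v 3 the figures are about 11% and 5%.

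The result turns on *p*. At *r* = 10% and 9 v 3, the chance at the unadjusted level runs from about 25% at *p* = 0.2 down to 2.6%, practically nominal, at *p* = 0.8.

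**The case against.** Several stronger readings are tempting, and the protocol does not support them.

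*That the AE comparison is biased.* All three arms share recordings at Day 3, Week 1 and Week 2, within a 14-day treatment period. YBT participants are assessed; the LOPM arms merely have extra occasions. Distortion needs events to be missed or forgotten between visits about 4 to 7 days apart, and nothing in the protocol shows that. Step 3 gives almost none when recall is good.

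*That every arm comparison is affected.* LOPM versus YBT + LOPM, the other primary contrast, has equal contact. In combination versus YBT, extra recording would raise the combination's count, which is conservative for a claim that the combination is safe. This stands, but conservatism does not help if an excess due only to recording is read as harm from adding LOPM.

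*That events after Week 2 are unobserved or in no arm's count.* Progressive muscle weakness, cauda equina syndrome and intractable pain are defined as serious events (Section 7.1). Serious-event and 24-hour AE reporting have no Week 2 cut-off, and pain and ODI are still measured to Week 26. What is absent is a routine prompt.

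*That Section 7.3 names the LOPM arms.* It does not. Treatment session is undefined, and the exercise routine in all arms also has sessions. Reading it as practitioner-delivered treatment is an inference, though a natural one, because the exercise routine is the participant's own and runs twice a day.

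It is also fair to say that recording events after a manual procedure is ordinary safety practice, and that ending routine recording with a 2-week treatment can be a design choice. Neither point resolves the conflict between sections or says which records feed the between-arm comparison.

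**Conclusion.** The contradiction is certain: the Summary with Sections 6.1 and 6.2, the study schedule, and Section 7.3 give three different rules for recording AEs, and no order of precedence. It should be corrected.

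The unequal contact is a consequence of following Section 7.3 as written alongside the schedule: 3 occasions for YBT alone against 6 to 9 in each LOPM arm. It rests on two assumptions: that treatment sessions are the practitioner-delivered ones, and that between none and three of them fall on visit days. It leaves comparisons with YBT alone open to ascertainment bias. The illustrative ratio of recorded rates runs from 1.01 to 1.77 according to an assumed pick-up probability, so the bias is possible but its presence and size are not established. LOPM versus YBT + LOPM is not affected.

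After Week 2 there is no routine AE recording for 24 of 26 weeks, although three visits fall in that time. Spontaneous and expedited reporting may still capture events, so this is a gap in systematic collection and not a period without observation.

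**What to change.** Reconcile the Summary, Sections 6.1, 6.2 and 7.3 and the study schedule to one rule:

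1. The between-arm comparison of AEs uses the same structured AE question, asked at the same visits in all three arms.
2. Events noted at LOPM sessions are still recorded, with a source flag, and are tabulated separately from the visit-based comparison.
3. AE recording is added at the existing Week 6, 14 and 26 visits.
4. The protocol states when AE collection and SAE collection each end.

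The between-arm comparison then rests on equal contact: 3 : 3 : 3 to Week 2 and 6 : 6 : 6 to Week 26.

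The cost is three more ticks at visits that already take place, one source field on the CRF and a few extra minutes per visit. No change to sample size, treatment or visit dates is needed.
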